### Patient and public involvement

Older persons living in Amsterdam were involved in the design of the AGCH concept. No patients were involved in the design of this study.

### Outcomes

The primary outcome measure is the 3-month unplanned readmission rate to the AGCH or hospital.

Secondary outcomes measured at 1, 3 and 6 months will include:

Activities of Daily Living (ADL)-functioning, as defined by the Katz-ADL scale.^36^Healthcare utilisation, including institutionalisation in a long-term care facility.Occurrence of delirium and/or falls.HRQOL.^37^All-cause mortality.Satisfaction of the patients and primary caregivers with the provided care.

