## Methods

### Setting

The AGCH opened in July 2018. It serves the south-eastern part of Amsterdam and its surrounding areas (an area with approximately 147 500 inhabitants).^28^ The AGCH is a 23-bed facility within a skilled nursing facility. The hospital has 24 hours geriatric and nursing assistance. Physiotherapy and routine laboratory testing are available during the workweek and simple X-ray is available once a week. The population that is eligible for admission to the AGCH are patients with a combination of an acute medical problem requiring hospitalisation (eg, pneumonia, exacerbation of heart failure or a urinary tract infection) and a geriatric condition (eg, delirium, cognitive impairment, falls, or functional impairment). Additionally, patients have to be haemodynamically stable and should not require complex diagnostic testing. In general, patients will not be admitted if they have the following exclusion criteria: (1) require care that can only be provided at an intensive care unit, (2) require surgery, (3) require urgent treatments or diagnostic tests that can only be provided in-hospital (eg, endoscopy, interventional radiology), (4) do not need hospital care but require transfer to a skilled nursing facility and (5) live in another region of the Netherlands.

Patients are directly admitted to the AGCH from the ED of the Amsterdam UMC-location Academic Medical Centre (AMC) in Amsterdam, which is a 1000-bed academic hospital with approximately 30 000 ED visits yearly. After the on-call geriatrician has assessed whether the patient is eligible for AGCH admission and the patient or representative has agreed to admission, the patient is transferred to the AGCH by ambulance. Since October 2019, patients can also be transferred from the EDs of other hospitals in Amsterdam. In the future, we plan to admit patients from home or general practice offices. Patients are admitted between 8.00 am and 23.00 pm, 7 days a week. At admission, a Comprehensive Geriatric Assessment (CGA) is conducted.^29^ The CGA gives an overview of all medical, functional, psychological and social problems. The CGA is discussed during multidisciplinary team meetings and used to formulate a care plan for each patient. For an overview of the admission process, the admission criteria and the components of this intervention, see figure 1.

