### Historical control groups

We selected two completed cohort studies that were conducted by our research group as historical control groups. We expect that the patients from these cohorts have similar admission diagnoses as those who can be admitted to the AGCH, namely, diagnoses that are ambulatory care sensitive conditions such as infections and exacerbations of chronic obstructive pulmonary disease (COPD) or heart failure.^32^ Patients in these two cohorts were admitted to internal medicine, cardiology, pulmonology and geriatrics departments. These departments admit patients with diagnoses similar to those that can be admitted to the AGCH. In addition, we have selected these cohorts as control groups as the patients come from the same area as the studied population admitted to the AGCH, that is, the greater Amsterdam area. The first control group from the Transitional Care Bridge Study consists of 674 patients who were recruited between September 2010 and March 2014.^33^ Participants were patients of 65 years and older hospitalised for at least 48 hours. Proxy consent was provided for participants suffering from severe cognitive impairment (MMSE ≤15). They participated in a negative randomised controlled trial that assessed the effectiveness of a nurse-led transitional care programme in preventing functional decline.^33^ The second control group from Hospital-Associated Disability and impact on daily Life study (Hospital-ADL study) consists of 401 patients who were recruited between October 2015 and June 2017.^10^ These participants were enrolled in a prospective cohort studying the trajectory of functional decline in older hospitalised adults. Participants were aged 70 years and older and were hospitalised for at least 48 hours. Patients suffering from severe cognitive impairment (MMSE ≤15) and delirium were excluded from participation. For the detailed methodology and inclusion criteria of the two control cohorts, please refer to the study protocols and papers of these studies.^10 33–35^

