### Data collection

Eligible patients and/or legal representatives will be contacted and informed about the study procedures after which written informed consent is obtained. Inclusion and interviewing of patients is conducted by an onsite researcher. Routine data on functioning and risk assessments are collected by a trained registered nurse and physiotherapist as part of the CGA for each patient.^38^
Table 1 gives an overview of measurement of the primary and secondary outcomes over time. These measurements were chosen based on the assessments and data collected from the two historic control groups. The online supplementary table provides an overview of the content and timing of measurements in the AGCH-group compared with the two historic control groups. Measurements during admission are at H1, which is within 48 hours after admission, and H2, which is within 48 hours before discharge. Follow-up is completed by telephone at 1, 3 and 6 months after discharge (P1, P3 and P6).

10.1136/bmjopen-2019-033802.supp2Supplementary data

**Table 1 T1:** Overview of the content and description of the (outcome) measurements and timing of the measurements at the acute geriatric community hospital (AGCH)

	Description and/or instrument	H1	H2	P1	P3	P6
1. Medical and demographical data						
Sociodemographic data	Date of birth, age at admission, sex, level of education, living conditions, marital status	R				
Data on admission	Time spent at the ED, admission diagnosis, date and time of admission	R				
Chronic conditions	Charlson Comorbidity Index^39^	R				
Polypharmacy	Number of drugs	R				
Mortality	Date of death		R	R	R	R
2. Cognitive functioning						
Cognitive impairment	Mini-Mental State Examination^31^	R				
Delirium	Safety management system patient screening (VMS)^42^ Confusion Assessment Method^40^ Delirium Observation Scale^43^	N/D	N/D			
3. Psychosocial functioning and quality of life						
Apathy	Geriatric Depression Scale^44^	N	R	R	R	R
Social network and informal care	Presence and frequency of informal care	R		R	R	R
Quality of life and health status	EQ-5D^37^	R		R	R	R
4. Physical functioning						
Identifying at-risk-patients	ISAR-HP—Identifying Seniors at Risk score^45^	N				
Functional status	Activities of Daily Living (ADL) modified Katz-ADL score^36^	N				
(Im)mobility	Using a walking aid, information from the Katz-ADL questions on exercise	N				
Handgrip strength	Jamar^49^	P				
Gait speed	Short Physical Performance Battery^50^	P				

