##### Delirium

The Confusion Assessment Method (CAM), four-item short version, is used to assess the presence and duration of delirium.^40^ The CAM is widely used by physicians and nurse practitioners to diagnose delirium (sensitivity of 53%–90% and specificity of 84%–100%).^41^ The CAM is filled out within 24 hours of admission. Moreover, the risk on developing delirium is assessed using the Dutch Safety Management Programme (*Veiligheidsmanagementsysteem (VMS*)) criteria for risk of delirium.^42^ Nurse practitioners will score the CAM daily from day 1 till day 3 of admission; if there are signs of possible delirium at day 3, these measurements are continued until the symptoms are resolved. In addition, during the first 3 days of admission, the Delirium Observation Screening Scale is scored during each nursing shift and is continued when there is a clinical suspicion of delirium.^43^

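### Delirium occurrence is not limited to new cases although one control cohort excluded delirious patients, and it is listed at follow-up times when delirium is not assessed

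*Protocol article*

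**What the plan says.** The Outcomes section of the protocol article introduces its list with "Secondary outcomes measured at 1, 3 and 6 months will include", and one item is "Occurrence of delirium and/or falls". Nothing in the article says whether delirium already present on arrival counts.

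On the AGCH side, the Setting section requires an acute medical problem together with "a geriatric condition (eg, delirium, cognitive impairment, falls, or functional impairment", among other examples. The Participants section lets delirious patients into the study through a legal representative. The Preliminary results name delirium among the admission diagnoses of enrolled participants.

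On the control side, the Historical control groups section describes two cohorts. For Hospital-ADL (401 patients) it states: "Patients suffering from severe cognitive impairment (MMSE ≤15) and delirium were excluded from participation". For Transitional Care Bridge (674 patients) it states no delirium exclusion and mentions proxy consent in severe cognitive impairment.

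On measurement, the Delirium section says "The CAM is filled out within 24 hours of admission" and "Nurse practitioners will score the CAM daily from day 1 till day 3 of admission", with continuation while symptoms last. The Delirium Observation Screening Scale is scored per nursing shift over the same first days. Table 1 marks the delirium instruments at H1 (admission) and H2 (discharge) only. P1, P3 and P6 are telephone contacts after discharge.

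**The concern.** The Introduction's reasoning concerns delirium that the hospital environment brings about. Delirium present on arrival cannot be an effect of the place of care. If any occurrence counts, AGCH patients who arrive delirious become outcome events, while Hospital-ADL could contribute no such events by design. The comparison then mixes the effect of care with a difference in who was allowed into each cohort.

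This outcome takes a place in the Hochberg family of secondary outcomes, so a distorted result would be tested and reported alongside the others. A real preventive effect could be hidden or, against Hospital-ADL, could appear with the wrong sign.

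The timing raises a second, separate problem. The planned multilevel models contain time and a time-by-group interaction, but the article describes no delirium values at 1, 3 or 6 months to put into them.

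**Working it through.** **No stated figure to reproduce.** The article gives no delirium rate and no sample size for this outcome. The rates below are assumptions; the cohort sizes come from the Historical control groups section.

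**Shares of the controls.** 674 + 401 = 1,075. Hospital-ADL is 401/1,075 = 37.3%; Transitional Care Bridge is 674/1,075 = 62.7%.

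**Formula.** Let p be the share delirious at entry and i the risk of new delirium among the rest. If every case counts, occurrence = p + (1 − p) × i.

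**Illustration with a true halving.** Assume p = 10% at the AGCH, and i = 5% at the AGCH against 10% in the controls.
- AGCH: 0.10 + 0.90 × 0.05 = 14.5%.
- Hospital-ADL (p = 0): 10%. The halving shows as an AGCH excess of 4.5 points.
- Transitional Care Bridge, if it also had p = 10%: 0.10 + 0.90 × 0.10 = 19%.
- Pooled controls in that case: 0.627 × 19% + 0.373 × 10% = 15.6%. The AGCH is then lower, 14.5/15.6 = 0.93, so a true halving shows as about a 7% relative reduction.
- Change of sign: pooled controls equal 0.10 + 0.627 × 0.90 × q, where q is entry delirium in Transitional Care Bridge. Setting this to 0.145 gives q = 0.045/(0.627 × 0.90), or about 8%. Below that the AGCH looks worse; above it the benefit shows with the right sign, though diluted at the 10% used above.

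**Range with no true effect.** Let p run from 5% to 30% at the AGCH and in Transitional Care Bridge, with p = 0 in Hospital-ADL and i from 5% to 10% everywhere.
- Excess over Hospital-ADL = p × (1 − i): from 0.05 × 0.90 = 4.5 points to 0.30 × 0.95 = 28.5 points.
- Excess over pooled controls = 0.373 × p × (1 − i): from 1.7 to 10.6 points.

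The pooled range depends on equal entry delirium in the AGCH and Transitional Care Bridge. The general pooled excess is (1 − i) × (p at the AGCH − 0.627 × q). It stays positive as long as q is below p/0.627, which is 15.9% when p is 10%.

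**Weighting.** The Planned statistical analyses section builds weights from covariates that differ at baseline or relate to 90-day readmission. A weight can only re-balance patients who exist, and Hospital-ADL has none delirious at entry. Cognitive score is no substitute, because the Cognitive impairment section says the MMSE is not done in patients delirious at inclusion.

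**Timing, source by source.**
- Outcomes: the whole list is placed at 1, 3 and 6 months.
- Data collection: those times are telephone contacts after discharge.
- Table 1: delirium is marked at H1 and H2 only, whereas falls, the other half of the same item, are marked at P1, P3 and P6.
- Delirium section: only scoring during admission is described.

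Empty cells in Table 1 would be weak evidence alone, since Katz-ADL also lacks follow-up marks there. For Katz-ADL, however, the Functioning level section says in prose that follow-up measurement takes place. Delirium has no such sentence, and its own section agrees with the table.

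**The case against.** **A reader might infer that the AGCH will necessarily look harmful**, for example with a 45% relative increase (14.5% against 10%). The documents do not support that. It holds against Hospital-ADL alone, or if Transitional Care Bridge had no delirium at entry. Transitional Care Bridge supplies 62.7% of the controls with no stated delirium exclusion, and at 10% entry delirium the pooled comparison favours the AGCH.

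**A reader might also take an entry prevalence from the Preliminary results**, using the 29.2% proxy consent (62/212) or the 25.1% with other diagnoses. Neither measures delirium. Proxy consent also covers cognitive impairment, and the diagnosis group also contains falls and unexplained functional decline.

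**Weighting is not useless everywhere.** The plan will assess balance and overlap, and the AGCH records an admission CAM. If Transitional Care Bridge recorded entry delirium, that cohort could supply overlap. This stands, but it does nothing for Hospital-ADL.

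**The definition may be in the full protocol or analysis plan**, neither of which is shown, and new cases can be derived from the admission and daily CAM. That is fair as far as missing detail goes. But the article itself fixes the outcome's wording, its timing and the control cohorts, and its limitations mention baseline differences only in general terms.

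**The exclusion sentence could mean both conditions together.** The natural reading is that either one excluded a patient.

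**The timing point is a loose list heading.** Largely true: satisfaction is under it too, yet Table 1 places it at discharge. The error is still on the page and is a matter of correction, with no evidence that it would distort a result.

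**Conclusion.** The point holds for one secondary outcome; the primary outcome is untouched. As worded, delirium at entry counts against the AGCH relative to a cohort selected to be free of it, and weighting cannot repair that for the 37.3% of controls from Hospital-ADL. With no true effect, the assumed ranges give a spurious AGCH excess of 4.5 to 28.5 points over Hospital-ADL. Against pooled controls it is 1.7 to 10.6 points if Transitional Care Bridge matches the AGCH in entry delirium. Whether a real benefit would be reversed or only masked in the pooled comparison depends on a rate the documents do not give. These are unadjusted illustrations. How delirium was measured in the controls cannot be checked, because the supplementary table is not shown.

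The timing contradiction is established from the text alone: as described, no delirium values at 1, 3 or 6 months will exist.

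**What to change.** 1. Define the outcome as new in-hospital delirium among patients without delirium at the admission assessment, which at the AGCH is the CAM within 24 hours.
2. Apply the same restriction to each control cohort where delirium at admission was recorded or was an exclusion. Leave out of this comparison any cohort where it cannot be established.
3. Report delirium at entry as a baseline characteristic, by cohort.
4. Remove delirium from the outcomes at 1, 3 and 6 months. Falls can stay there as a separate item.

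**Cost.** On the AGCH side this is a change of wording, because the admission CAM is already collected. On the control side someone must check what was recorded about delirium at admission in both completed cohorts. If Transitional Care Bridge has no usable record, the comparison rests on Hospital-ADL alone. Patients delirious at entry drop out of this one outcome.

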### Data collection

Eligible patients and/or legal representatives will be contacted and informed about the study procedures after which written informed consent is obtained. Inclusion and interviewing of patients is conducted by an onsite researcher. Routine data on functioning and risk assessments are collected by a trained registered nurse and physiotherapist as part of the CGA for each patient.^38^
Table 1 gives an overview of measurement of the primary and secondary outcomes over time. These measurements were chosen based on the assessments and data collected from the two historic control groups. The online supplementary table provides an overview of the content and timing of measurements in the AGCH-group compared with the two historic control groups. Measurements during admission are at H1, which is within 48 hours after admission, and H2, which is within 48 hours before discharge. Follow-up is completed by telephone at 1, 3 and 6 months after discharge (P1, P3 and P6).

10.1136/bmjopen-2019-033802.supp2Supplementary data

**Table 1 T1:** Overview of the content and description of the (outcome) measurements and timing of the measurements at the acute geriatric community hospital (AGCH)

	Description and/or instrument	H1	H2	P1	P3	P6
1. Medical and demographical data						
Sociodemographic data	Date of birth, age at admission, sex, level of education, living conditions, marital status	R				
Data on admission	Time spent at the ED, admission diagnosis, date and time of admission	R				
Chronic conditions	Charlson Comorbidity Index^39^	R				
Polypharmacy	Number of drugs	R				
Mortality	Date of death		R	R	R	R
2. Cognitive functioning						
Cognitive impairment	Mini-Mental State Examination^31^	R				
Delirium	Safety management system patient screening (VMS)^42^ Confusion Assessment Method^40^ Delirium Observation Scale^43^	N/D	N/D			
3. Psychosocial functioning and quality of life						
Apathy	Geriatric Depression Scale^44^	N	R	R	R	R
Social network and informal care	Presence and frequency of informal care	R		R	R	R
Quality of life and health status	EQ-5D^37^	R		R	R	R
4. Physical functioning						
Identifying at-risk-patients	ISAR-HP—Identifying Seniors at Risk score^45^	N				
Functional status	Activities of Daily Living (ADL) modified Katz-ADL score^36^	N				
(Im)mobility	Using a walking aid, information from the Katz-ADL questions on exercise	N				
Handgrip strength	Jamar^49^	P				
Gait speed	Short Physical Performance Battery^50^	P				
Falling	Fall history Falls in the AGCH Numeric Rating Scale (NRS) on the fear of falling^35^	N N	R R	R R	R R	R R
Pain	NRS on pain^51^	N	R	R	R	R
Fatigue	NRS on fatigue^52^	N	R	R	R	R
Nutrition	Short Nutritional Assessment Questionnaire^53^	N				
5. Healthcare utilisation and satisfaction with care						
Medical care during admission	Diagnostics performed in the AGCH Readmission to university hospital Length of stay at the AGCH		R			
Hospital readmission	Readmission rate to the hospital or AGCH		R	R	R	R
Healthcare utilisation	Home care, medical specialist care, temporary institutional care, primary care	R		R	R	R
Satisfaction with care	8-question questionnaire^54^		R	(R)*		

*In case the assessment was missed at H2.

AGCH, Acute Geriatric Community Care Hospital; D, Doctor/attending physician; ED, emergency department; EQ-5D, EuroQoL-5D; H1, at admission; H2, at discharge; ISAR-HP, Identification of Seniors at Risk-Hospitalized Patients; N, nurse; P1, one month after discharge; P3, three months after discharge; P6, six months after discharge; P, physiotherapist; R, researcher/research nurse.

Data collection includes the following.

#### Medical and demographical data

##### Sociodemographic data

These will include age, gender, highest level of education, ethnicity, marital status and living arrangement.

##### Data on admission

Time spent at the ED, admission diagnosis and date and time of admission.

##### Chronic conditions

The number and severity of chronic conditions will be assessed using the Charlson Comorbidity Index.^39^ This index is commonly used to indicate the risk of mortality; each condition is scored 1, 2, 3 or six points, with a higher total number of points indicating a greater risk of death.

##### Polypharmacy

Polypharmacy will be assessed by counting the number of individual drugs that are chronically prescribed to a participant, in which a number of five or more drugs is considered polypharmacy.

##### Mortality

This will be assessed during follow-up, either from the patients’ electronic files or from general practice registries.

#### Cognitive functioning

##### Cognitive impairment

This is assessed by reviewing the score of the MMSE that is performed within 48 hours of admission. The MMSE includes 23 items (total score 0–30) that screen for cognitive impairment. A score of 23 or less is defined as possible cognitive impairment.^31^ When a patient is delirious on inclusion, the MMSE is not conducted.

##### Delirium

The Confusion Assessment Method (CAM), four-item short version, is used to assess the presence and duration of delirium.^40^ The CAM is widely used by physicians and nurse practitioners to diagnose delirium (sensitivity of 53%–90% and specificity of 84%–100%).^41^ The CAM is filled out within 24 hours of admission. Moreover, the risk on developing delirium is assessed using the Dutch Safety Management Programme (*Veiligheidsmanagementsysteem (VMS*)) criteria for risk of delirium.^42^ Nurse practitioners will score the CAM daily from day 1 till day 3 of admission; if there are signs of possible delirium at day 3, these measurements are continued until the symptoms are resolved. In addition, during the first 3 days of admission, the Delirium Observation Screening Scale is scored during each nursing shift and is continued when there is a clinical suspicion of delirium.^43^

#### Psychosocial functioning and quality of life

##### Apathy

We use three items of the *Geriatric Depression Scale* (GDS-15) to assess apathy (sensitivity of 69% and specificity of 85 %). These items include the following questions: (1) ‘Do you prefer to stay at home, rather than going out and doing new things’, (2) ’Have you dropped many of your activities and interests?’ and (3) ‘Do you feel full of energy’. A score of >2 points is classified as ‘apathy present’.^44^

